## Methods

### Study Setting

This study is designed as a prospective, experimental, multicenter, 3-cohort investigation. The research will be performed at Albacete University Hospital Complex, Spain (with the coordinating Clinical Research Ethics Committee; hospital 1); Getafe University Hospital, Spain (hospital 2); and primary care units of Donostialdea, Osakidetza, Spain (primary care units). The primary health care units involved in the study will be located in 2 districts/regions of Gipuzkoa: the region of Donostialdea and the region of Tolosaldea. The design of this study protocol, characterized as exploratory, adheres to the SPIRIT (Standard Protocol Items of the Recommendations for Interventional Trials; Multimedia Appendix 1) 2013 guidelines, as depicted in Figures 1 and 2.

**Figure 1 figure1:**
[figure not shown]
SPIRIT (Standard Protocol Items of the Recommendations for Interventional Trials) figure.

**Figure 2 figure2:**
[figure not shown]
Flow diagram of the study protocol.

### Study Population Recruitment

#### Hospital Exercise Cohort

Participants will be consecutively recruited from the scheduled patient list of the falls unit and the outpatient clinics of hospital 1. Upon obtaining informed consent, patients will undergo a baseline clinical evaluation. Subsequently, ultrasound measurements and a DXA scan will be conducted, and blood samples will be collected, processed, and stored. These patients will then be enrolled in a 16-week multicomponent physical exercise program (discussed later). Following the completion of the exercise program, at the 16-week follow-up, a repetition of clinical evaluation, ultrasound, DXA, and blood-sample testing will be performed.

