Sarcopenia and frailty, although connected and associated with aging, are distinct conditions. Sarcopenia primarily centers around the musculoskeletal system, while frailty is a more multifactorial condition [28,29]. Various studies indicate that the prevalence of sarcopenia among older adults with frailty is higher than the prevalence of frailty among those with sarcopenia [28,30-32]. Adverse outcomes linked to muscular decline can be mitigated, delayed, or even reversed through early detection and interventions, including nutritional support and physical exercise programs [13,18,33]. Nonetheless, there exists a need for straightforward and dependable tools that facilitate the assessment of muscle quality and its implications for frailty [28,34].

Ultrasound, as a fast, noninvasive, and cost-effective imaging modality, is gaining rapid prominence for musculoskeletal examination [35,36]. Currently, clinical ultrasound images (B-mode) enable the assessment of muscle mass and morphology, encompassing measures such as muscle thickness, pennation angle, cross-sectional area, echo intensity, and fascicle length [37-39]. Despite ongoing efforts for standardization, these measurements remain highly reliant on the expertise and skills of the operator, and they do not provide definitive results for the early staging of muscle quality loss [37,40]. Ultrasound morphometric measurements of sarcopenia in older adults have demonstrated mild to moderate associations with frailty [41]. More recently, various quantitative ultrasound techniques have surfaced, involving the analysis of echogenicity, texture parameters, elastography, and acoustic wave properties. However, their translation to clinical practice is still limited [42-51]. Artificial intelligence is presenting new opportunities to objectify musculoskeletal ultrasound, with recent studies showcasing automatic muscle segmentation, fiber angle detection, and textural discrimination of muscle microstructures [52-55].

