#### Hospital Control Cohort

Participants will be consecutively recruited from the scheduled patient list of the frailty unit, day hospital, and the outpatient clinic of the Geriatrics Department of hospital 2. Upon obtaining informed consent, baseline study variables will be collected. These patients will be followed up for 16 weeks under usual care. After the follow-up period, a repetition of the baseline evaluation will be conducted.

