### Randomization and Blinding

Data analysis will be conducted independently of cohort recruitment and follow-up. The evaluation of data will take place at the Deusto Institute of Technology (Ultrasound Data Evaluation Center) and Biodonostia (Blood-based Assays Evaluation Center). Initially, only anonymized data, including ultrasound images, raw data, and blood-based assays, will be transmitted to the data evaluation centers. In the case of combination models, a training set of clinical variables will also be transferred to the data evaluation centers. Reserved data sets will be kept at the clinical acquisition centers for independent testing. This includes data from various sites and information obtained during follow-up examinations.

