### Outcomes

#### Primary Outcomes

Investigating the association between quantitative ultrasound biomarkers related to muscle mass and quality (thickness [mm], cross-sectional area [cm^2^], perimeter [mm], pennation angle [degrees]) extracted from raw data and blood-based biomarkers, as well as their combinations with clinical variables. These clinical variables encompass frailty (FRAIL [short 5-question assessment of Fatigue, Resistance, Aerobic capacity, Illnesses, and Loss of weight] scale ranging from 0 to 5, with 0 indicating robustness and 5 indicating frailty, and Frailty phenotype by Fried et al [4], ranging from 0 [robust] to 5 [frail]), sarcopenia (SARC-F [Strength, Assistance with walking, Rising from a chair, Climbing stairs, and Falls] scale scores ranging from 0 [robust] to 10 [sarcopenic]), physical function (Short Physical Performance Battery [SPPB] Scale score ranging from 0 to 12, where 0 indicates the lowest physical performance and 12 indicates the highest performance), International Physical Activity Questionnaire scores ranging from 0 (lowest) to 3 (highest), Gait Speed Test in seconds, grip strength measured by Jamar dynamometer in kilogram, disability (Global Deterioration Scale, consisting of 7 stages), Barthel Index (ranging from 0 [total dependent] to 100 [independent]), Lawton and Brody Index (scores from 0 [dependent] to 8 [independent]), nutritional status (Mini Nutritional Assessment—Short Form), body composition (DXA), and quality of life (EQ-5D-5L) within 3 cohorts of older adults: hospital control cohort, hospital exercise cohort, and primary care cohort.

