### Evaluation of Quantitative Ultrasound Biomarkers

#### Morphometric Ultrasound Measures

Throughout the examination, the sonographer will record morphometric ultrasound measurements using the online ultrasound scanner’s interface (Figure 5). This includes capturing the thickness of the rectus femoris in the transverse view at the midsection point, measuring the perimeter and cross-sectional area of the rectus femoris in the transverse view, and determining the pennation angle in the longitudinal view.

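### In the hospital exercise cohort, baseline ultrasound follows the clinical evaluation and nothing keeps the sonographer unaware of the scores, so operator-dependent primary measures can be recorded with frailty status known

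*Protocol article*

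**What the plan says.** The subsection on the hospital exercise cohort gives a sequence for the baseline visit: "Upon obtaining informed consent, patients will undergo a baseline clinical evaluation", and then "Subsequently, ultrasound measurements and a DXA scan will be conducted, and blood samples will be collected, processed, and stored". At 16 weeks "a repetition of clinical evaluation, ultrasound, DXA, and blood-sample testing will be performed"; the clinical evaluation is listed first, but no word fixes the order. The hospital control subsection says only "Upon obtaining informed consent, baseline study variables will be collected", and the primary care subsection says the same, so neither states an order.

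Under Morphometric Ultrasound Measures, during the examination "the sonographer will record morphometric ultrasound measurements using the online ultrasound" scanner's interface. The values are rectus femoris thickness, perimeter, cross-sectional area and pennation angle. Primary Outcomes names the same four quantities and sets them against FRAIL, the frailty phenotype, SARC-F, SPPB, gait speed, grip strength and other clinical variables. On conventional B-mode morphometry the Introduction says that "these measurements remain highly reliant on the expertise and skills of the operator".

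Under Randomization and Blinding, "Data analysis will be conducted independently of cohort recruitment and follow-up", and the evaluation centers at first receive anonymized data only. That section does not mention the sonographer.

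**The concern.** The primary question is whether ultrasound and blood measures agree with the clinical assessment of frailty, sarcopenia and function. In such a comparison the index measure should be read without knowledge of the reference result. Here, in one cohort, the stated order puts the reference first, and nothing described prevents its result from reaching the person who chooses the frame and places the calipers.

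If readings lean even slightly toward the known status (a frail participant's muscle measured a little thinner, for example), the lean appears in the analysis as a biomarker-frailty association. Anonymized transfer to the evaluation center does not correct it, because the recorded values already carry it. It can also travel further: Raw Data Evaluation uses the sonographer's annotations as a guide for the offline regions of interest, and Table 1 trains the segmentation models on those annotations.

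The preliminary results show why a small lean could matter. In Table 3 the correlations of muscle area with the frailty phenotype (r = -0.211) and with SARC-F (r = -0.236) are weak.

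**Working it through.** **The text, step by step**

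1. Order: clinical evaluation and then ultrasound at baseline in the hospital exercise cohort, which is 50 of the 200 planned participants (Sample Size). It is not stated for the other 150.
2. Subjectivity: four measures recorded live by the sonographer, of a kind that the Introduction describes as operator-dependent.
3. Role: the same four measures are named in the primary outcome.
4. Masking: stated for the analysis and the evaluation centers, not for the scan.

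It follows that the sonographer can know the reference result. It does not follow that the sonographer does: the article says neither who performs the clinical evaluation nor whether its scores are passed on.

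**Possible size**

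The plan gives no figure for reading bias, so there is none to reproduce. The tilt b below, a systematic reading difference between frail and robust in SD units, is assumed.

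With no true difference, a two-sided 5% test of frail against robust has standard error SE = sqrt(1/n1 + 1/n2) and shift d = b/SE. It rejects with probability 1 - Φ(1.96 - d) + Φ(-1.96 - d).

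*Within the exercise cohort.* Sample Size expects 85% frail and 15% healthy in the hospital cohorts. Of 50 participants that is 42.5 and 7.5, so SE = sqrt(1/42.5 + 1/7.5) = 0.396.

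*All three cohorts pooled and all exposed.* Frail: 0.85 × 100 + 0.15 × 100 = 100. Robust: 100. SE = sqrt(2/100) = 0.141.

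| Assumed tilt (SD) | d, exercise cohort | Rejection, exercise cohort | d, all 200 exposed | Rejection, all 200 exposed |
|---|---|---|---|---|
| 0.05 | 0.126 | 5.2% | 0.354 | 6.4% |
| 0.10 | 0.252 | 5.7% | 0.707 | 10.9% |
| 0.20 | 0.505 | 8.0% | 1.414 | 29.3% |

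Sample Size also projects 139 robust and 86 frail. Those counts give 6.5%, 11.3% and 30.8% in the last column, which changes nothing of substance.

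*All 200 analyzed, only the exercise cohort exposed.* A 0.20 SD tilt confined to the readings of frail participants dilutes to 0.20 × 42.5/100 = 0.085 SD. If it is split evenly between frail and robust readings, it dilutes to 0.10 × 42.5/100 + 0.10 × 7.5/100 = 0.05 SD. With 100 against 100 the rejection rates are 9.2% and 6.4%.

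**The case against.** The strongest reply is that the article nowhere says that the sonographer performs, sees or is told the clinical scales, or that everything happens at one sitting. Staff roles are often left to the full protocol, and this article condenses one. That stands as a limit: the exposure is possible, not shown. It does not dispose of the point, because the order is stated and the masking that is stated stops short of the scan.

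Four stronger readings are tempting, and the document does not support them.

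- *The whole study is affected, with a false-positive rate near 29%.* That needs a 0.20 SD tilt in all 200 participants, 150 of whom have no stated order.
- *Reversing the order would remove the problem at no cost.* Recruitment from a falls or frailty unit suggests likely status whatever the order, and at follow-up the baseline results already exist. If one person does both tasks, reversal moves the exposure to the clinical assessor. Eligibility also depends on the Barthel score, cognition and ability to do the functional tests, so scanning first could mean scanning people later found ineligible.
- *Muscle and blood are sampled after exertion from the functional tests.* No timing is given, so this cannot be inferred.
- *Nothing can be recovered later.* At least 12 coregistered B-mode and raw frames are kept per examination, the primary outcome text describes its ultrasound measures as derived from raw data, and automatic morphometry is planned. The protection is partial: frame choice remains, and the annotations guide the regions of interest and train the segmentation. The blood assays are run at a separate center on anonymized samples, so caliper placement cannot affect them.

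**Conclusion.** The point holds in a limited form. For 50 of 200 participants the stated baseline order allows operator-dependent primary measures to be recorded with the reference result known, and no stated safeguard prevents it. For the other 150 the order is open. The threatened quantity is the cross-sectional association of the live morphometric measures with frailty and function, in the direction of inflation.

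The size is unknown. Under an assumed tilt of 0.05 to 0.20 SD, the false-positive rate is about 5% to 8% within the exercise cohort. The 29% figure is an upper illustration that requires exposure of everyone. These rates rest on the expected 85/15 split, a normal approximation and a tilt for which the document gives no source. The modest size within one cohort does not argue against acting, since the change is inexpensive and the observed associations with the frailty and sarcopenia scales are weak.

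**What to change.** Going forward:

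- Complete the eligibility checks, then take the baseline ultrasound frames and measurements, then administer the scored frailty scales and performance tests. State this one order for all three cohorts.
- State that clinical scores are withheld from the sonographer, and ultrasound values from the clinical assessor, at both visits. At follow-up this matters more than order, because baseline results already exist.

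For participants already measured (Table 3 reports baseline data on 66 of the 100 planned hospital participants), record the order used. Examine the primary association by order rather than simply excluding those scanned second, which could remove most of the hospital participants and with them most of the expected frail group. Also compare it with the association from the planned automatic morphometry on the stored frames. That check is not fully independent for the cross-section, because its segmentation is trained on sonographer annotations.

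The cost is a changed visit worksheet and a sentence on masking, an occasional scan of someone later found ineligible, and a mixed order across participants. If one person now does both tasks at a site, withholding results would need a second person. Some exposure will remain, because the recruitment unit and any eligibility results, such as the Barthel score, may still be known.

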#### Hospital Control Cohort

Participants will be consecutively recruited from the scheduled patient list of the frailty unit, day hospital, and the outpatient clinic of the Geriatrics Department of hospital 2. Upon obtaining informed consent, baseline study variables will be collected. These patients will be followed up for 16 weeks under usual care. After the follow-up period, a repetition of the baseline evaluation will be conducted.

#### Primary Care Cohort

Participants will be consecutively recruited from the scheduled patient list of the primary care units. Upon obtaining informed consent, baseline study variables will be collected. These patients will be followed up for 1 year under usual care. After the 1-year follow-up, a repetition of the baseline evaluation will be conducted.

Recruitment is conducted by the study coordinator staff at each site, under the overall supervision of the clinical principal investigator at each site. Participants will sign the informed consent at the beginning of the first visit. The professional overseeing the assessment will provide an explanation of the project, and the participant will sign both the information sheet and the informed consent to participate. The principal investigator at each site will be responsible for collecting and monitoring the documentation related to informed consent. The inclusion and exclusion criteria are listed in Textbox 1.

Inclusion, exclusion, and termination criteria.
**1. Inclusion criteria**
Age of at least 70 years.Either gender.Ability to provide informed consent.Ability to perform all the functional tests.In the hospital exercise cohort, the ability to participate in the physical exercise program.
**2. Exclusion criteria**
Expected survival of <1 year.Barthel Scale score <70.Moderate-to-severe cognitive impairment.Refusal to participate.Medical conditions that may compromise or impede follow-up assessments.Older adults already enrolled in regular physical exercise programs will be excluded from participating in the hospital exercise cohort.
**3. Termination criteria**
Refusal to continue participation.Complications during or in between examinations and intervention.

### Allocation

The allocation sequence in this multicentric study is institution-based. Patients recruited at the Department of Geriatrics of the Complejo Hospitalario Universitario de Albacete will be automatically allocated to the supervised exercise program by default. By contrast, patients recruited at the Geriatrics Department of the University Hospital of Getafe will not be assigned to any specific interventions. Similar sociodemographic characteristics are anticipated for both patient populations. At each institution, patients will be recruited from the falls unit, outpatient clinics, and day hospital. Within each acquisition site, patient selection will be conducted based on the clinical agenda until the recruitment goals are met.

The allocation sequence is sequential, aligned with the clinical agenda, and overseen by the clinical principal investigator at each site. Any deviations from the recruitment plan outlined in the clinical agenda must be thoroughly justified and meticulously documented.

### Interventions

In the hospital exercise cohort, a 16-week supervised multicomponent physical exercise program will be implemented. The individualized exercise intervention, tailored to each individual’s functional capacity, comorbidities, and previous experience, will consist of 2 supervised sessions per week, each lasting 45 minutes. These sessions will be conducted in small groups, with 4-6 older adults per group. The sessions are divided into warm-up, main part (strength, power, and coordination exercises), and cool down (flexibility and stretching). The main part of the exercise program comprises 8 exercises targeting the major muscle groups. The progression starts with low-intensity and high-volume sessions, gradually advancing to higher intensities and lower volumes. Depending on the stage, participants will complete 2-4 sets, consisting of 4-15 repetitions, with a 30-second rest between sets and exercises. For each exercise, loads and intensities will be adjusted to achieve a total of 30 repetitions. All exercise sessions are to be conducted in the gym of the Geriatrics Department of the hospital. Participants will be encouraged to incorporate additional 90-minute walks per week into their routine. It is important to note that the exercise program is aligned with the guidelines of the VIVIFRAIL program [67], which specifically aims to prevent weakness and reduce the risk of falls.

In the hospital control and primary care cohorts, no specific intervention will be implemented.

### Retention

In alignment with the VIVIFRAIL program guidelines, our intervention program is designed to prevent weakness and reduce the risk of falls. Patients will be informed about the program’s benefits during recruitment and follow-up. Within the supervised exercise program, interventions and patient progress will be personalized and monitored, taking into account functional capacity, comorbidities, and the individual’s previous experiences. The sessions will be closely monitored at the gym of the Geriatrics Department of the hospital. The individualized sessions will enable discussions on progress with the patient throughout the intervention, fostering motivation for retention and completing the follow-up. Participants will also be encouraged to adopt healthy habits, such as incorporating an additional 90-minute walk per week. In case participants require medical care that may interfere with the ongoing study procedures, they will be managed according to the clinical routine and subsequently excluded from the study. In these cases, the data collected during the baseline examination will be used for a cross-sectional clinical evaluation of frailty and sarcopenia. However, musculoskeletal changes following the multicomponent exercise program will not be assessed.

### Safety Monitoring

Each principal investigator at every data acquisition center will oversee the monitoring and follow-up of participants included in their respective cohorts under usual care. They will make decisions regarding patient exclusion and assignment to interventions, and monitor termination criteria as deemed necessary. Additionally, participation in an exercise program is generally associated with a low risk (–1%) of adverse events [68], most of which are typically low-grade responses to exercise, such as muscle soreness [69]. However, in the event of adverse events or serious adverse events, they will be promptly reported to the Clinical Research Ethics Committees.

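### Safety Monitoring gives site investigators a decision on assignment that Allocation makes automatic by institution, leaving room for selection at hospital 1 in the secondary exercise comparison

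*Protocol article*

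**What the plan says.** The Allocation section sets the rule: "The allocation sequence in this multicentric study is institution-based". Patients recruited in geriatrics at hospital 1 (Albacete) "will be automatically allocated to the supervised exercise program by default". Those recruited at hospital 2 (Getafe) "will not be assigned to any specific interventions". The investigator's part in that section is oversight: "The allocation sequence is sequential, aligned with the clinical agenda, and overseen by the clinical principal investigator at each site". A safeguard follows: "Any deviations from the recruitment plan outlined in the clinical agenda must be thoroughly justified and meticulously documented".

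Safety Monitoring describes a wider role. Each centre's principal investigator "will oversee the monitoring and follow-up of participants included in their respective cohorts under usual care". The next sentence reads: "They will make decisions regarding patient exclusion and assignment to interventions, and monitor termination criteria as deemed necessary". It gives no criteria for deciding on assignment.

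Four other places bear on the point:

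- **Interventions** gives the 16-week programme to the hospital exercise cohort alone.
- **Textbox 1** has an inclusion criterion for that cohort only: "In the hospital exercise cohort, the ability to participate in the physical exercise program". It also bars people already in regular exercise programmes from that cohort only.
- **Retention** removes from the study participants who need medical care that interferes with study procedures. It keeps their baseline data for the cross-sectional evaluation and does not assess their change after exercise.
- **Secondary Outcomes** and **Statistical Analysis** plan a direct comparison of the two hospital cohorts, 50 patients with the intervention against 50 without.

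**The concern.** The exercise comparison is not randomised. Its protection against choosing individual patients is that they are taken in the order of the clinical agenda and that the recruiting hospital settles what they receive. If assignment is automatic, nobody has anything to decide. If an investigator decides it, it is not automatic.

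The discretion is not symmetric between the arms. Hospital 1 has a programme that can be withheld from an enrolled patient, and hospital 2 has none. Any use of the discretion therefore changes who counts as an exercise patient without a matching change among the controls. The Limitations section acknowledges bias only if the populations of the two institutions differ, and it plans a post hoc look at their characteristics. Selection among enrolled patients within hospital 1 is a different matter.

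**Working it through.** The protocol gives no figure on this point, so there is none to reproduce. The main check is to read the sections against each other.

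**Step 1. Who settles assignment?** Under Allocation, the recruiting institution does, and the investigator oversees the sequence. Under Safety Monitoring, the investigator does. Overseeing a fixed sequence is not the same as deciding assignment.

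**Step 2. Where can the discretion act?** Interventions provides no specific intervention in the hospital control and primary care cohorts, so a decision on assignment has no object there. The power to exclude is written for every centre, but only at hospital 1 can it turn on the exercise programme. The literal effect is that a hospital 1 patient may be left out of exercise, or out of the cohort, after enrolment. Nobody can be moved between hospitals.

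**Step 3. Is the investigator unaware of assignment?** No. Assignment is by institution, so site staff know it. Randomization and Blinding separates data evaluation from recruitment and does not change that.

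**Step 4. Is this the only route for selection?** No. The two exercise-only criteria in Textbox 1 act before enrolment, and the Retention exclusion acts after it. The Safety Monitoring sentence adds a further route, and unlike the others it has no stated criterion.

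**Step 5. Which analyses are exposed?** The between-hospital comparison of change is exposed. The primary outcome is cross-sectional association, and under Sample Size and Retention baseline measurements stay in it when follow-up is missing.

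**Step 6. Illustration of size (inputs assumed, not in the document).** Suppose a share e of hospital 1 patients, those lowest on some trait, drops out of the comparison, and the trait has correlation ρ with the outcome. With q the normal quantile at e, the mean of those remaining shifts by

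shift = ρ × φ(q) / (1 − e), in SD units.

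| e | φ(q)/(1 − e) | ρ = 0.1 | ρ = 0.3 | ρ = 0.5 |
|---|---|---|---|---|
| 5% | 0.109 | 0.011 | 0.033 | 0.054 |
| 10% | 0.1755/0.90 = 0.195 | 0.019 | 0.058 | 0.097 |
| 20% | 0.2800/0.80 = 0.350 | 0.035 | 0.105 | 0.175 |

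If ρ is negative, the signs reverse.

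For scale, 50 against 50 with 80% power and two-sided α of 0.05 detects (1.960 + 0.842) × √(2/50) = 0.560 SD (0.566 with the t distribution). The shifts run from 0.011/0.560 = 2% to 0.175/0.560 = 31% of that. The protocol's own 0.284 for this objective is not used as the yardstick. It matches a one-sample or paired test on 100 (2.802/√100 = 0.280, or 0.283 with t), not two groups of 50. That is a separate matter.

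**The case against.** The best defence is that the sentence is loose wording, not a second allocation rule. It stands under Safety Monitoring, follows a sentence about each investigator's own cohort, and is paired with termination criteria. The Allocation rule is itself expressed as a default, gives the investigator oversight, and asks for deviations from the recruitment plan to be justified and documented. On this reading the investigator applies eligibility, carries out the site's own assignment and handles safety withdrawals. This is plausible and softens the conflict. It does not remove it: Allocation does not say who may depart from the default or why, and its documentation rule concerns recruitment by the clinical agenda.

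A reader might also infer stronger points that the document does not support:

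- **That investigators would select by expected tolerance or response.** Safety Monitoring names no such ground. Selection on ability to exercise is already explicit in Textbox 1, so this sentence adds to it and does not open it.
- **That exercise would be favoured by 0.20 or 0.35 SD.** Those are shifts in baseline fitness if exactly the least fit 10% or 20% were removed. The outcome here is change, and the least fit may have more or less room to improve, so the direction is open too.
- **That the bias could not be corrected.** Under Hospital Exercise Cohort, baseline assessment comes before entry to the programme, and Statistical Analysis plans regression on covariates. Measured differences could be partly adjusted for. Unmeasured reasons could not.
- **That no record of such decisions would be kept.** The article condenses a fuller protocol, and operational logging may be set out there.

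**Conclusion.** The point holds as a conflict of wording with a limited statistical consequence. Allocation and Safety Monitoring need to be reconciled. Until they are, a hospital 1 investigator who knows the assignment may, on a literal reading, withhold exercise from an enrolled patient or remove that patient, and no matching decision exists at hospital 2.

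The exposed analysis is secondary, non-randomised and has one hospital per arm, in a study that calls itself exploratory. The primary cross-sectional outcome is not affected. The document gives neither the frequency of such decisions nor their relation to the outcome, so neither the size nor the direction of any bias can be derived. The range of about 0.01 to 0.18 SD rests wholly on the assumed 5% to 20% left out and the assumed correlations of 0.1 to 0.5. The correction is worth making because it closes an avoidable route for selection at little cost.

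**What to change.** 1. In Safety Monitoring, remove the reference to deciding assignment, and state that assignment follows the recruiting institution as set out under Allocation.
2. For the hospital comparison, analyse every enrolled participant with available follow-up in the cohort of the recruiting hospital, whether or not exercise was received.
3. Reconcile that rule with Retention, which now excludes some participants after enrolment and drops their change data. Without this step the new rule would conflict with Retention.
4. Report, by hospital, the number of and reasons for exclusions and for non-receipt of exercise.

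Clinical decisions on stopping exercise stay with the investigators, and nothing is proposed about them here.

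The cost is a few sentences in two sections and a count by hospital. The abstract gives June 30, 2024 as the end of recruitment. If recruitment is complete, items 2 to 4 can still be settled before the comparison is run. The statistical price is some dilution. For example, if 5 of the 50 exercise patients did not exercise and had no benefit (both assumed), the estimate would be 45/50 = 90% of the effect in those who did. The exercise-only eligibility criteria remain, so the fix removes this added route and not all selection on ability to exercise.
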